## Methods

### Study design

This is a national, prospective, multicenter, open-label, randomized phase II study with two parallel groups, with the participating hospitals being located in the state of North Rhine-Westphalia in the proximity of Düsseldorf (a list of participating centers can be obtained from the sponsor or the registry). In the active recruitment period of 30 months, 136 patients with newly diagnosed, isocitrate dehydrogenase (IDH) wildtype, primary GBM [55] will be randomized at a 1:1 ratio after near-complete resection and successful production of tumor lysate. For a patient to be enrolled, all eligibility criteria (see below) must be met and free vaccine production capacity has to be available (enrollment may have to be paused). Enrollment of a patient is initiated by an investigator submitting by fax the Randomization Request Form to the Coordination Center for Clinical Trials, which will perform the randomization and inform the investigator of the outcome and allocation of the patient to the control or the vaccination arm of the study. The randomization list has been generated by the Coordination Center for Clinical Trials, using randomly selected block sizes of 4, 6, 8 and 12 patients. It will be centrally applied with concealment by the Coordination Center for Clinical Trials. The assignment to the two groups will be stratified according to O6-methylguanine-DNA-methyltransferase promotor methylation status, because it is an independent prognostic factor in TMZ chemotherapy [2, 56].

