In the control group, patients receive this standard treatment with proven clinical efficacy (comparator). Patients in the vaccination arm of the study will receive as add-on up to seven tumor lysate-loaded, mature DC vaccines (2–10 × 10^6^ cells each applied by intradermal injection): four priming vaccines in weekly intervals during the period between concomitant radiochemotherapy and adjuvant chemotherapy and three monthly boosting vaccines in the third week of the first three 28-day cycles of adjuvant TMZ (Fig. 1). Availability of less than three vaccines is regarded as treatment failure. Vaccines will be applied irrespective of whether concomitant TMZ has to be terminated or adjuvant TMZ has to be reduced or terminated due to toxicity. Corticosteroids should be avoided or kept to a minimum 1 week before until 1 week after vaccination. In case of temporary need for high-dose corticosteroids 1 week before vaccination (> 8 mg/day dexamethasone or equivalent), vaccination has to be postponed. Any other anti-cancer treatment, including agents with only suspected anti-cancer effects, any other investigational or experimental treatment, any other active immunotherapy or any treatment that interferes with immune function, including persistent immunosuppressive therapy (e.g., for rheumatism) should be avoided or kept to a minimum during the treatment period. If a patient misses two or more of the priming vaccinations, this is regarded as treatment failure. If one priming vaccination or one, two or all three boost vaccinations are missed, it will be attempted to add the missed vaccinations (maximum: 3) as additional boost vaccinations, always in the third week of subsequent adjuvant TMZ cycles (cycles 4–6).

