### Eligibility criteria

All inclusion and exclusion criteria (Table 1) will be evaluated by the local investigators (neurosurgeons and/or neuro-oncologists) and in case of residual tumor volume after surgery and diagnosis/tumor cell content of tumor sample confirmed by central neuroradiologist and neuropathologist, respectively.

**Table 1 Tab1:** Inclusion and exclusion criteria

Key inclusion criteria	Key exclusion criteria
Newly diagnosed, monofocal GBM, isocitrate dehydrogenase wildtype (WHO grade IV; [57]) histologically confirmed by central neuropathologist	Medical history of severe acute or chronic disease with poor prognosis, autoimmune disorder, immunodeficiency, organ allograft or prior malignancy (≤ 3 years)
Near-complete resection (≤ 5 ml residual tumor volume) confirmed by central neuroradiologist on magnetic resonance imaging (MRI) scan within 72 h postoperative	Infection with human immunodeficiency virus, hepatitis B virus, hepatitis C virus or *Treponema pallidum* or other severe infection requiring hospitalization or i.v. antibiotics or anti-viral treatment (≤ 2 weeks)
Patients ≥ 18 years of age	Known allergy or intolerability to TMZ or any component of the capsules, dacarbazine, the contrast agent or the DC vaccine
Karnofsky performance status ≥ 70%	History of bleeding diathesis or coagulopathy
Sterile tumor sample of ≥ 150 mg with tumor cell frequency ≥ 60%, as determined by central neuropathologist, available for vaccine production	Preexisting myelosuppression
Successful production of sterile, avital tumor lysate	Previous radiotherapy to head and neck
Systemic corticosteroids tapered down to ≤ 2 mg of dexamethasone or equivalent per day within 7 days postoperative	Previous (≤ 6 weeks. or ≤ 5 half-lives) treatment with specific immunostimulatory agent
Adequate hepatic, renal, liver and bone marrow function and blood coagulation	Previous (≤ 4 weeks) treatment with live, attenuated vaccine
Use of highly effective contraception	Treatment of GBM in another clinical trial with therapeutic intervention or current use of any investigational agent
Signed informed consent	Known pregnancy or breast-feeding
	O6-methylguanine-DNA-methyltransferase promoter methylation status equivocal

Legend: *DC* dendritic cell, *GBM* glioblastoma multiforme, *i.v.* intravenous, *TMX* temozolomide, *WHO* World Health Organization

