Evaluation of results will be based on the Statistical Analysis Plan. Efficacy is measured by OS computed from the day of surgery until event or censored at last follow-up according to the Kaplan-Meier method with two-sided log-rank statistics for comparison. Primary efficacy analysis will be based on the intention-to-treat population; patients lost to follow-up are censored at the time of last contact. If required, a model-based Bayesian analysis for imputation of missing data will be used, and missing values imputed using the posterior predictive distribution of the model. In addition, a sensitivity analysis based on the per-protocol population will be performed.

All patients will be evaluated for safety; assessment of safety will be based on descriptive and explorative methods. For explorative analyses of secondary endpoints, classical statistical tests will be applied (e.g., log-rank test for survival data (PFS), chi-square/Fischer’s exact test for categorical data and *t* test/Mann-Whitney *U* test for continuous data). In addition, 95% confidence intervals will be calculated when applicable.

A Cox regression model will be used for explorative analysis of overall survival and progression-free survival with the covariates (1) treatment group, (2) recursive partitioning analysis classes I–IV as defined by Mirimanoff et al. [69] and de Vleeschouwer et al. [70], which already have been documented to influence outcome of standard as well as of vaccination therapy, the prognostic markers, (3) MGMT promotor methylation status, (4) extent of resection (complete vs. near-complete), (5) age, (6) center, (7) dexamethasone medication and (8) the therapeutic intervention in case of tumor progression. Subgroups of vaccinated patients will also be defined based on their immunological responsiveness as well as immunosuppressive scores (see below).

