## Discussion

### Trial design

The trial design attempts to minimize parameters, which have been identified to affect clinical and immunological outcome, in order to generate informative results on efficacy of DC vaccination in GBM. Only adults with confirmed newly diagnosed primary GBM after near-complete resection will be included, with all patients undergoing standard radio/TMZ chemotherapy. Moreover, DC vaccination with high-purity, tumor-lysate-loaded, mature DC will be fully integrated into standard therapy.

Randomization will be the main method against bias. DC vaccines are produced specifically for the individual patient, using the patient’s own tumor and leukocytes as starting material. We have considered it to be unethical to subject the patients of the control group to the potential risks and the stress of leukapheresis merely for blinding purposes. Thus, only patients of the vaccination group are subjected to leukapheresis and, therefore, there will apparently be different procedures applied to patients in the control and vaccination groups, which also requires different logistics. Therefore, blinding the study has not been possible.

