### MRI and pseudoprogression

Standard radiochemotherapy of GBM may result in a transient increase in contrast enhancement in a large fraction of patients, which will subside eventually without any change in therapy [59]. Therefore, early MRI diagnostics at week 10 after completion of radiochemotherapy is not feasible. Similarly, immunotherapy may result in inflammatory reactions, which mimic tumor progression and may even include the appearance of “new lesions” on MRI scans [60]. This pseudoprogression, irrespective of whether due to standard radiochemotherapy or immunotherapy, is difficult to differentiate from true tumor progression. Moreover, immunotherapy may result in delayed responses, i.e. patients may still benefit from therapy although showing signs of progressive disease initially [60]. To minimize premature declaration of tumor progression and discontinuation of therapy, in the situation of suspected progression, thus when patients meet the radiological RANO criteria for progression initially, patients may continue study medication until progression has been confirmed on a subsequent MRI scan performed within 4–6 weeks [59]. However, there still may be uncertainty regarding progression. Due to the sometimes long-lasting nature of particularly immune-related effects, distinguishing progression from pseudoprogression unequivocally can require a prolonged (≥ 3 months) observation period as summarized by Okada et al. [60]. Therefore, subsequent confirmatory MRI scans in 4–6-week intervals will be performed and patients can continue study medication as long as the clinical and neurological status of the patient has not been worsening substantially and the study medication is well tolerated, does not interfere with therapeutic interventions for imminent complications, and the investigator assesses an overall possible clinical benefit [60]. Re-operation will be considered, to allow for final histological confirmation of tumor progression [59, 60], if the suspected lesion if surgically accessible and it is the investigator’s medical judgement that the patient may benefit from re-operation as reported previously [108, 109]. The use of additional imaging techniques (e.g., fluoroethyl-tyrosine positron-emission tomography (FET-PET)) to confirm MRI findings is also possible. The exact time of progression is defined retrospectively, when pseudoprogression and pseudoresponses can be excluded. Further treatment in case of progression is at the discretion of the investigator.

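### The explorative Cox models for OS and PFS adjust for treatment given at progression, which arises after randomisation and, for PFS, only once the event has occurred

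*Protocol article*

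**What the plan says.** In the protocol article, under Sample size considerations and statistical analysis, one sentence covers both outcomes: "A Cox regression model will be used for explorative analysis of overall survival and progression-free survival with the covariates". Treatment group is item (1). Prognostic factors follow, and the list closes with "6) center, (7) dexamethasone medication and (8) the therapeutic intervention in case of tumor progression". The article does not say that item (8) applies to OS only, or how it is coded.

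Three other places fix the timing and nature of item (8):

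- Study design: patients "will be randomized at a 1:1 ratio after near-complete resection and successful production of tumor lysate", which is before radiochemotherapy and long before progression can be assessed.
- MRI and pseudoprogression: "Further treatment in case of progression is at the discretion of the investigator".
- Trial design, in the Discussion: "blinding the study has not been possible".

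The confirmatory analysis is separate. "Primary efficacy analysis will be based on the intention-to-treat population", and it uses Kaplan-Meier estimates with a two-sided log-rank test. PFS is compared by log-rank test among the explorative secondary analyses.

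**The concern.** A covariate in a model meant to give an adjusted treatment effect should be fixed at or before randomisation. Item (8) is not.

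For PFS the problem is logical. Only a patient who has already had the event can have a value for treatment at progression, so the covariate carries the outcome into the predictor side of the model.

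For OS the variable lies downstream of progression, which the vaccine is meant to delay, and unblinded investigators choose it. Holding it constant removes or distorts part of the pathway through which the vaccine could act, and it can bring in differences between arms in how relapse is managed. Readers will see a treatment-group coefficient listed beside known prognostic factors and take it for the adjusted vaccine effect.

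**Working it through.** **Step 1: the plan's own figures.** Medians of 14.6 and 26.6 months give HR = 14.6/26.6 = 0.549 and ln HR = -0.5999. By Schoenfeld's formula, d = 4(1.960 + 0.8416)² / 0.5999² = 4 × 7.849 / 0.3599 = 87.2. The article states 87, and power at 87 events is 79.9%. With 10% dropout, 122/0.90 = 135.6, so 136 as stated. Nothing here uses the Cox covariates.

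**Step 2: the PFS model, by logic.** PFS is taken as time to progression or death. Let Z be treatment at progression.

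- *Z as a fixed covariate.* Z = 1 implies that the patient progressed under observation. Every patient with Z = 1 has an event, and every censored patient has Z = 0. Z then predicts the event by construction.
- *Z as a time-dependent covariate.* Just before each event time, every patient at risk is still progression-free, so Z(t) = 0 for all of them. The factor exp(γZ) equals 1 in every term of the partial likelihood, and γ cannot be estimated.
- *Z as type of therapy.* Patients without progression need a category for none, which is the first case again. If they are left missing, the model is confined to patients who had the event.

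**Step 3: the OS model, by logic.** Coded as fixed, Z = 1 guarantees survival to progression. Coded as time-dependent, that timing fault goes, but the model still conditions on something that the vaccine can change.

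**Step 4: illustrative size.** The documents give no progression or salvage rates, so all of the following are assumptions:

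- exponential times and 1:1 allocation
- control median 7 months to progression and 7 months from progression to death
- death hazard before progression 0.005 per month, not affected by the vaccine
- treatment at progression halves the later death hazard and has no effect on PFS
- censoring uniform over 24-54 months
- Z coded yes/no and fixed

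Each row shows 10 runs of 4,000 patients. The first column gives the true vaccine HR on progression and on death after progression. The arrows give the vaccine HR without and then with Z.

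| True HR | Treated at progression, vaccine / control | OS | PFS | Apparent PFS HR of Z |
|---|---|---|---|---|
| 1 / 1 | 50% / 50% | 0.99 → 0.99 | 0.99 → 0.99 | 1.20 |
| 1 / 1 | 70% / 40% | 0.88 → 1.01 | 1.00 → 0.95 | 1.21 |
| 1 / 1 | 40% / 70% | 1.18 → 1.02 | 1.00 → 1.05 | 1.20 |
| 0.55 / 0.55 | 50% / 50% | 0.47 → 0.45 | 0.57 → 0.58 | 1.42 |
| 0.55 / 0.55 | 70% / 40% | 0.41 → 0.44 | 0.57 → 0.53 | 1.53 |
| 0.55 / 0.55 | 40% / 70% | 0.56 → 0.47 | 0.56 → 0.63 | 1.41 |
| 0.55 / 1 | 60% / 60% | 0.71 → 0.68 | 0.57 → 0.59 | 1.47 |

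Higher use shifts PFS more. With 90% treated in both arms, the PFS HR moved from 0.58 to 0.63. With 70% of vaccinated and 90% of control progressors treated, it moved from 0.59 to 0.68. The apparent PFS HR of Z reached about 2.4, although Z had no effect on PFS.

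At the trial's size (136 patients, 600 runs), the scenario with true HR 0.55 and 40% / 70% use gave a PFS treatment effect significant at 5% in 88.0% of runs without Z and 67.5% with it. With 70% / 40% use the share rose instead, from 87.0% to 91.8%.

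**The case against.** **The models are explorative.** This stands and sets the weight of the point. Neither log-rank test uses a covariate, and nor do the sample size and the interim rule. A reader might infer that the primary result is compromised; it is not. The label does not make the PFS coefficient interpretable, however.

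**The statistical analysis plan may settle the coding.** For OS, a time-dependent coding there could remove the timing fault. For PFS, Step 2 shows that no coding helps, so this is a stated choice and not a detail left to another document.

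**Later therapy is a legitimate question for OS.** It is. In the two rows with no vaccine effect and unequal use, the whole OS difference comes from later therapy, and adjustment brought the HR close to 1. That answers a different question from the randomised comparison. It belongs in a separate analysis with its own label.

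**Dexamethasone.** A reader might infer that item (7) has the same fault. The documents do not show this. No time point is given, and a baseline value could exist, because eligibility requires steroids tapered to no more than 2 mg "of dexamethasone or equivalent per day within 7 days postoperative". A time point would still help, because the later guidance, "Corticosteroids should be avoided or kept to a minimum 1 week before until 1 week after vaccination", concerns only the vaccine arm.

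**Direction and extremes.** A reader might infer that adjustment always dilutes the vaccine effect. The table shows shifts both ways, and none with no vaccine effect and equal use. A reader might also expect an infinite estimate if every progressor is treated. That needs no deaths at all before progression; at the assumed 0.005 per month, the apparent HR of Z was finite, about 4.5. Whether this is the only multivariable analysis planned cannot be known without the analysis plan.

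**Conclusion.** The point holds for item (8). In the PFS model it is invalid as written, whatever the coding. In the OS model it means that the treatment-group coefficient does not estimate the randomised vaccine effect. These two conclusions rest on the order of events in the article and need no assumed rates.

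The size does rest on assumptions. Across the scenarios with a true effect on progression and 40-90% of progressors treated, a PFS HR of about 0.56-0.59 became 0.53 to 0.68. The OS HR moved either way, for example 0.56 to 0.47 and 0.41 to 0.44. Other progression times, salvage rates or codings would give other figures.

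This should be corrected before the analysis, at moderate to low priority. The explorative adjusted estimates are at stake, and the trial's main conclusion is not.

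**What to change.** - Delete item (8) from the PFS Cox model.
- Delete it from any OS Cox model used to report an adjusted treatment effect.
- Tabulate treatment after progression by arm.
- If its association with OS is of interest, fit a separate model with it as a time-dependent covariate, and state that the result is not a causal estimate of either the vaccine or the later therapy.
- As a clarification only, state that item (7) is dexamethasone at randomisation.

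The cost is wording in the protocol and analysis plan. The number of events, number of patients and primary test stay as they are, and no further data are needed. Make the change before results by arm are known, so that it cannot look driven by the data.

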## Discussion

### Trial design

The trial design attempts to minimize parameters, which have been identified to affect clinical and immunological outcome, in order to generate informative results on efficacy of DC vaccination in GBM. Only adults with confirmed newly diagnosed primary GBM after near-complete resection will be included, with all patients undergoing standard radio/TMZ chemotherapy. Moreover, DC vaccination with high-purity, tumor-lysate-loaded, mature DC will be fully integrated into standard therapy.

Randomization will be the main method against bias. DC vaccines are produced specifically for the individual patient, using the patient’s own tumor and leukocytes as starting material. We have considered it to be unethical to subject the patients of the control group to the potential risks and the stress of leukapheresis merely for blinding purposes. Thus, only patients of the vaccination group are subjected to leukapheresis and, therefore, there will apparently be different procedures applied to patients in the control and vaccination groups, which also requires different logistics. Therefore, blinding the study has not been possible.

### Tumor-induced immunosuppression

After activation by the DC, effector T cells can cross the blood-brain barrier and exert their effector function in the brain [71], with a contribution of luminal antigen presentation by endothelial cells to identify the specific site for effector T cells to enter the brain parenchyma [54] and a final tuning of T-cell effector functions by the brain microenvironment [71, 72]. Thus, the basic pre-requisites for DC vaccination therapy of GBM are in place, and numerous animal studies could confirm that it is a a promising therapeutic approach in brain tumors [73–77]. However, there is also tumor-induced immunosuppression, and several contributing mechanisms have been identified [78, 79], including an increase in regulatory T cells in the blood as well as in the tumor microenvironment, which is associated with impaired T-cell responsiveness [80]. Such immunosuppression may hamper DC vaccination therapy and, therefore, has to be overcome, to improve or even allow efficacy. In GBM, it correlates with the size of the tumor, and surgical cytoreduction can restore T-cell responsiveness, at least partially [81–84]. Certain chemotherapeutics, including TMZ, which is used in the standard treatment of GBM, have also been reported to reduce T_reg_ in the periphery as well as in the tumor [50–52], which might be important to increase the vaccine efficacy [85, 86]. Thus, there is a rationale to maximally reduce the tumor burden, prior to DC vaccination therapy and combine it with TMZ chemotherapy.

### Lysate as a source of tumor antigens

For the GlioVax trial, autologous tumor lysates are used as a whole-tumor cell source of tumor antigens. Even when high-purity tumor tissue is collected by FSG, there is an abundance of normal self-proteins in tumor lysates. Nevertheless, induction of autoimmunity or other severe side effects attributable to the use of lysates for vaccine production have not been reported. Therefore, lysates can be considered a safe source of tumor antigens.

Lysates most likely will contain multiple tumor antigens, which are present in the individual tumor of a patient (including the various cellular subsets within the tumor), i.e. the patient’s full antigenic repertoire, ensuring antigenic diversity, thereby reducing the risk of escape of tumor-antigen-loss variants [87]. Since the respective proteins are endogenously processed in the DC, presentation on HLA-class I and II molecules is possible and independent of the HLA type of the patient, thereby allowing induction of cytotoxic as well as T_H-_responses at the same time, which is a pre-requisite for the development of an efficient cytotoxic T-cell response. Furthermore, lysate may provide in addition to the tumor antigens the necessary signals for guiding effector T cells to the brain [88]. Whether lysates are superior to molecularly defined tumor antigens in inducing anti-tumoral immune responses or more beneficial clinically in GBM is currently unknown. However, Neller et al. concluded from the analysis of 173 published immunotherapy trials on various tumor entities, including melanoma, renal cell and hepatocellular carcinomas, lung, prostate, breast, colorectal, cervical, pancreatic and ovarian cancers, a higher objective response rate (8.1% vs. 3.6%) when whole-tumor-cell antigens compared to molecularly defined tumor antigens were used [89]. Therefore, lysates represent an immunologically potent source of tumor antigens.

